### 9.3 Reporting procedures

The Investigator will complete an SAE report form and forward by fax to the North and East Yorkshire R and D Alliance immediately (within 24 hours) of becoming aware of an SAE.

#### Contact details for reporting SAEs and SUSARs

In the case of a SAE, complete a SAE report form and forward by fax to the North and East Yorkshire R&D Alliance within 24 hours of becoming aware of the SAE.

Fax numbers:

**North and East Yorks R&D Alliance: [name]**

#### 9.3.1 Follow-up

In the event of an SAE, the participant will be followed up by the Investigator until completion of the event or until a decision is made by the Sponsor to cease follow up.

In the event of withdrawal due to an SAE or AE, the Investigator will follow up the participant until completion of the event or until a decision is made by the Sponsor to cease follow up.

#### 9.3.2 Ongoing and end of trial reporting

At the conclusion of the study all AEs/ARs, occurring during a study must be subject to statistical analysis and that analysis and subsequent conclusions will be included in the final study report.

One year following the granting of a Clinical Trials Authorisation Certificate, and thereafter annually, the CI will send an annual safety report to the:

- Sponsor
- Medicines and Healthcare products Regulatory Agency (MHRA).
- Research ethics committee that granted approval.

In addition, the CI will provide annual progress reports to the research ethics committee and report to the Sponsor as required.

#### 9.3.3 Pregnancy reporting

Should a pregnancy occur in a participant during the trial then this pregnancy will be reported to the Sponsor as an SAE and the pregnancy will be followed up by the CI in accordance with North and East Yorkshire R and D Alliance procedure.

## **9.4 Withdrawal of participants from the study**

The participant is free to withdraw from the study at any time, without giving a reason, and without their clinical care being affected.

### **9.4.1 Interruption of dosing**

Interruption of dosing describes a temporary cessation of study gel use. Interruption of dosing will occur in the presence of:

- a grade 2 or above solicited genital adverse event
- any clinical event at the discretion of the CI which should lead to discontinuation of study gel

Dosing may be recommenced after interruption following an adverse event at the discretion of the CI.

### **9.4.2 Discontinuation of dosing**

Discontinuation of dosing describes a permanent cessation of study gel use. Discontinuation of dosing will occur in the presence of:

- a grade 3 or above solicited genital adverse event
- a grade 3 or above clinical or laboratory event
- any clinical event at the discretion of the CI which should lead to discontinuation of study gel

Interruption or discontinuation of gel use may also occur if the participant desires to stop study gel use. Wherever possible, participants who discontinue study gel use either by choice or following advice will continue to adhere to the follow up schedule up to the final visit.

### **9.4.3 Withdrawal from the trial**

Withdrawal from the trial means discontinuation of both study visits and study gel. The reasons for withdrawal (if available) and any efforts made to contact the participant after loss of contact or non-attendance should be recorded in the participant's file. Examples for study withdrawal include:

- participant desire to stop participating in the trial
- Investigator concerns that continuing visits is not in the best interest of the participant
- decision taken to discontinue the trial in all participants

### **9.4.4 Samples and analysis after withdrawal**

If a participant is considered a screen failure, discontinues dosing or withdraws from the study at any time, either by choice or on the recommendation of clinical personnel, data and samples collected up to that point will remain available for analysis as part of the study. Participants' anonymised tissue samples will be stored and analysed as per the study protocol.

### **9.4.5 Follow-up of participants after withdrawal**

In the event of withdrawal due to an SAE or AE, the Investigator will follow up the participant until completion of the event.

## **9.5 Temporarily halting or stopping the study**

In the case of 3 women experiencing either a grade 3 or above genital adverse event or grade 3 or above clinical or laboratory adverse event, the study will be temporarily halted pending unblinded review by the Data Monitoring Committee (DMC). Several severe or

serious AEs, which are probable in relation to the study gel, will lead to the study being terminated at that point. The decision to stop the study rests on the CI, with recommendations from the DMC (see section 11.6.3).

The Sponsor reserves the right to terminate the study at any time.

## 10. STATISTICS AND ANALYSIS

### 10.1 Sample size

As this is the first administration in humans intravaginally, there is no information to carry out power calculations. This study will provide some information to help such calculations in future studies.

### 10.2 Planned statistical analyses

Analysis will be carried out according to a detailed statistical analysis plan.

#### 10.2.1 Initial subject characteristics

All demographic (age, height, weight) and other baseline subject characteristics (physical examination, concomitant diseases) will be tabulated and analysed descriptively.

#### 10.2.2 Statistical analyses of primary and secondary endpoints

Antibody levels in vaginal Weck-Cel samples, cervico-vaginal lavage and serum samples will be summarised for each treatment group as minimum, median, and maximum at each time-point. Treatment groups will be compared using the Kruskal Wallis test corrected for ties. Where the Kruskal Wallis test is statistically significant,  $P < 0.05$ , the two active treatment groups will be compared using a Mann Whitney U test, to check whether there is evidence that the higher dose produces higher antibody concentrations.

Half-life will be estimated for each antibody using only the groups which received an active dose, and observations at 1, 8, and 24 hours after the first dose. The method will be to assume an exponential decay curve. If we cannot assume this, a half-life is not a meaningful estimate. A log transformation of the observed concentration will be used and an analysis of covariance model fitted with time as continuous predictor and participant as a categorical factor. Two checks on the assumptions will be made. Linearity will be checked by including and testing a time squared term. Uniformity of the half life will be checked by testing an interaction between time and participant. If the assumptions are met, half-life will be estimated by  $\log(2)/\text{slope}$ . The 95% confidence interval will be found from the usual confidence interval for the slope. If assumptions are not met, analysis will then be data-driven.

All analyses of antibody levels will be carried out using the raw data and Weck-Cel antibody concentrations will also be analysed using data adjusted for the dilution factor. All "not detectable" observations will remain "not detectable" and will not be adjusted. The dilution factor will be calculated as

$(\text{volume of processing buffer} + \text{Weck-Cel sample volume}) / \text{Weck-Cel sample volume}$

Adjustment for the dilution factor will be to multiply the observed antibody concentration by this dilution factor. Volume of processing buffer will be 600 microlitres.

Analysis of the safety endpoints will involve comparing counts of adverse event rates in the three groups using negative binomial regression.

Comparisons will be made for the following:

- Number of grade 3 or above solicited genital adverse events or events attributable to the study gel leading to discontinuation of gel (Appendix 6) during the dosing or follow up period

- Number of grade 3 or above other clinical or laboratory adverse (Appendix 7) events confirmed at examination or on repeat testing respectively during the dosing or follow up period
- All adverse events (irrespective of assigned relationship to study gel)
- All adverse events classed as possibly or probably treatment-related.

Details of sub-study analyses are provided in section 12.

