### 5.4 Trial interventions – research and control

Participants will receive vaginal microbicide gels containing either (a) high-dose monoclonal antibodies (b) low dose monoclonal antibodies, or (c) a control placebo vaginal microbicide gel. Gels containing either the high or low dose MAbs are referred to as 'the IMP' in this protocol; when referring to either the IMP or the placebo, the term 'study gel' is used. For more details of the study gels refer to section 8. A placebo arm is included in the study to increase the validity of safety endpoint analyses and investigate the impact of the IMP on vaginal flora (see sections 5.5.2 and 12.1).

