### **6.3 Number and source of participants**

We will aim to recruit and randomise 30 healthy HIV negative female volunteers. All 30 participants will be randomised to one of the three trial arms, subject to complete fulfilment of the eligibility criteria.

Participants will be recruited by advertising in the York area, including via the GU medicine clinic, the University of York, York St John University, mailing lists, and by coverage and advertising in local media.

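### The dose comparison is gated on a three-group Kruskal-Wallis test that includes the antibody-free placebo arm, so for well-detected vaginal levels the gate opens whatever the dose effect and limits nothing

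*Protocol*

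**What the plan says.** Protocol section 10.2.2 covers Weck-Cel, cervico-vaginal lavage and serum antibody levels. Minimum, median and maximum are reported per group at each time-point. Then "Treatment groups will be compared using the Kruskal Wallis test corrected for ties". Where that test gives P < 0.05, "the two active treatment groups will be compared using a Mann Whitney U test", and the stated purpose is "to check whether there is evidence that the higher dose produces higher antibody concentrations".

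The first test is not limited to the active arms. The half-life analysis in the same section is: "Half-life will be estimated for each antibody using only the groups which received an active dose". Table 8-1 gives the placebo gel zero antibody content, and section 5.4 explains why it is there: "A placebo arm is included in the study to increase the validity of safety endpoint analyses", together with the vaginal flora question. Section 10.2.2 also keeps non-detectable values as non-detectable. Section 6.3 sets the size: "We will aim to recruit and randomise 30 healthy HIV negative female volunteers", allocated 1:1:1 (section 10.3.1).

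**The concern.** A gate before a pairwise comparison is useful if it tends to stay closed when the pairwise difference is absent. Here one of the three groups has no source of antibody, so its samples are expected to tie at the bottom of the ranking. For vaginal levels the three-group test then mainly shows that antibody gel contains antibody. The dose question passes to a series of Mann-Whitney tests over antibodies, time-points, sample types and raw or dilution-adjusted data. None of these is named as principal, and section 10.2.2 attaches no effect size or confidence interval to the dose comparison. Section 10.1 says the study should inform later sample-size calculations, and a p-value alone does not supply what they need.

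Serum raises a different issue. Section 4 makes any systemic absorption part of the primary objective. If only a minority of women have detectable serum antibody, neither the three-group p-value nor the group median describes that well.

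**Working it through.** The protocol gives no power or expected effect to reproduce. Inputs from the document: 30 women, 1:1:1, gate threshold 0.05, three antibodies, five Weck-Cel times, two lavage times and two serum times (sections 5.5.1 and 5.5.2). Assumptions: exactly 10 per arm, no missing samples, placebo all non-detectable, two-sided Mann-Whitney tests, lognormal levels.

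**1. Gate with all active women detectable and no dose effect.** Placebo occupies ranks 1 to 10 (rank sum 55). The active arms share ranks 11 to 30. If they alternate, their rank sums are 210 and 200.
- H before tie correction = 12/(30×31) × (210²/10 + 200²/10 + 55²/10) − 3×31 = 19.42.
- Tie correction = 1 − (10³ − 10)/(30³ − 30) = 0.963.
- H = 19.42/0.963 = 20.16, and on 2 df p = exp(−20.16/2) = 0.00004.

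The least significant result possible has active rank sums of 205 each: H = 20.09, p = 0.000043. With full detection the gate cannot close.

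**2. Gate with partial detection.** Simulated pass rates with the same detectable share in both active arms:

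| Share detectable | Gate opens |
|---|---|
| 30% | 29% |
| 40% | 57% |
| 50% | 83% |
| 70% | 99.6% |
| 80% or more | 100% |

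In the macaque study (section 3.3.2) all three antibodies were detectable to 72 h and in the microgram range to 24 h. The lowest assay standard is 1.563 ng/ml (sections 10.4.1 to 10.4.3). High detection in the first 24 h is therefore the expected case. Human detection 36 h after dose 12, and in lavage, is unknown.

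**3. Effect on one dose test.** With full detection and log-SD 1 (assumed), high-versus-low Mann-Whitney rejects in 4.6% of trials at dose ratio 1 and 29% at ratio 2. The figures are identical with and without the gate.

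**4. Repeated tests.** Raw Weck-Cel: 3 × 5 = 15. With adjusted data 30; adding lavage (3 × 2 = 6) and serum (3 × 2 = 6) gives up to 42, many on the same or correlated data. If the 15 were independent, the chance of at least one false positive would be 1 − 0.95¹⁵ = 54%. With an assumed between-woman SD of 0.8 and within-woman SD of 0.95 on the log scale, simulation gave 29% to 38%, depending on how far residuals are shared across antibodies.

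**5. One summary per woman.** Under the same SDs and a true 2-fold ratio (log 2 = 0.693):
- one time-point: SD = √(0.8² + 0.95²) = 1.24, simulated power about 20%;
- mean log level over five times: SD = √(0.8² + 0.95²/5) = 0.91, simulated power about 34%.

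**6. Serum, 4/10 high, 4/10 low, 0/10 placebo.** The 22 non-detects tie at rank 11.5. If the eight detections split evenly, the rank sums are 175, 175 and 115. H = 3.097/0.606 = 5.11, p = 0.078. If the four high-dose values are the largest, p = 0.068. Six of ten values in each active arm are non-detectable, so both medians read not detectable.

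**7. Pooled Fisher as a replacement.** For 8/20 versus 0/10 it gives p = 0.029. For 4/10 high, 0/10 low, 0/10 placebo, Kruskal-Wallis gives H = 8.87, p = 0.012, but pooled Fisher (4/20 versus 0/10) gives p = 0.27.

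**8. Exact intervals.** For 0/20 active women, the upper 95% limit is 1 − 0.025^(1/20) = 17%. If 10% of active women truly have detectable antibody, the chance of seeing at least one is 1 − 0.9²⁰ = 88%.

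**The case against.** The strongest reply is that nothing is harmed. Section 10.2.2 assigns the dose question to the Mann-Whitney test, not to the gate. Each such test keeps its level, and no power is lost when levels are detectable. Dose superiority is not a listed objective. The main retention estimate, half-life, uses active arms only and has a 95% CI. This is a 30-woman first intravaginal study, and section 10.2 defers detail to a statistical analysis plan. Placebo may also be a useful assay control, since the C2F5 and C4E10 assays detect with a general anti-human IgG antibody and background signal is not excluded.

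Most of this stands, and it limits the point. A reader might infer that the gate biases the dose test; step 3 shows that it does not. A reader might also infer that the gate is always passed; step 2 shows that it can close when about half or fewer of the active women are detectable. The assay-control argument supports describing placebo levels, not ranking them in a gate.

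The deferral to an analysis plan does not answer the point. The protocol itself fixes the test, the threshold and the follow-up, and a plan that follows it inherits them.

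**Conclusion.** The point holds in a limited form. Where most active women are detectable, the gate carries no information on dose and does not limit false positives over the 15 or more dose tests: roughly 30% to 40% for at least one among the 15 under SDs that are assumed, not taken from the protocol. It is redundant, not biasing. The gain on offer is real but modest: for a 2-fold ratio, power of about 34% instead of 20%, three tests instead of 15, and an estimate with an interval.

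For serum, a reader might infer that absorption would be missed, or that pooling the active arms in a Fisher test would be more sensitive. The document supports neither as a general statement. The maximum is reported whatever the gate shows, so any detection appears there, and a closed gate blocks only the dose comparison. Pooling loses power when absorption occurs mainly at the high dose (step 7). What remains is that a p-value of about 0.07 and medians of not detectable are a poor summary of 8 of 20 active women with antibody in serum.

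**What to change.** Amend section 10.2.2 as follows.
- Remove the Kruskal-Wallis gate and describe placebo levels only.
- For each antibody, pre-specify one high-versus-low comparison of each woman's mean log Weck-Cel concentration (or log AUC from 1 to 24 h), reported as a geometric mean ratio with 95% CI. State how non-detectable values enter the calculation and whether raw or dilution-adjusted data are principal.
- Keep results at single time-points, and for lavage, descriptive.
- For serum, report the number and proportion of women with detectable antibody in each arm, with exact 95% CIs. Do not substitute a pooled Fisher test.

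The change is to analysis wording only; samples, visits and numbers are unaffected. The cost is fewer p-values at individual time-points and the need to commit to a rule for non-detects in advance.

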### **3.5 Rationale for study objectives**

This trial is being conducted to assess the pharmacokinetics and safety of the monoclonal antibody combination when applied vaginally. As the antibodies have already been given systemically to HIV infected men and women without any serious adverse events, and the gel formulations using the same components are sold as over-the-counter products (Replens® vaginal lubricant), we have every expectation that the IMP will be safe when applied vaginally.

The primary objective of the study is therefore to understand the pharmacokinetics of the antibody combination when applied vaginally, as this will guide us in terms of future development of the monoclonal antibody combination. Specifically we need to know how long the antibodies persist in the lower female genital tract, as this will inform recommended dosing frequency for development of the microbicide. The a priori hypothesis is that the monoclonal antibodies will not be systemically absorbed because of their relatively large molecular weight. No systemic absorption was detected after repeated application to rabbits. However, recent data in macaques shows very low (nanogram range) systemic absorption of the antibodies when applied vaginally, so this provides the rationale to study this directly in healthy females. We will also monitor systemic and local safety parameters, including haematology, biochemistry and genital adverse events. The formal list of outcome measures is presented in section 5.5.

In summary, administration of C2F5, C2G12, and C4E10 to male and female HIV-infected patients has been judged to be safe and well-tolerated by the investigators in all human clinical trials conducted to date and there are no overt safety concerns with regard to vaginal administration of the MABs to healthy, sexually abstinent female volunteers. The primary objective of this study is to assess the persistence of the MABs in the vagina and the systemic absorption at two different doses.

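### The half-life model fits one common slope to both active dose arms, so the rate of decline is neither estimated nor compared by randomised dose

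*Protocol*

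**What the plan says.** Protocol section 10.2.2 fixes the half-life analysis in some detail.

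- Data: "Half-life will be estimated for each antibody using only the groups which received an active dose", with "observations at 1, 8, and 24 hours after the first dose".
- Model: log concentration, with "an analysis of covariance model fitted with time as continuous predictor and participant as a categorical factor".
- Checks: a squared time term for linearity, and for the slope "Uniformity of the half life will be checked by testing an interaction between time and participant".
- Result: "If the assumptions are met, half-life will be estimated by" log(2) divided by the slope, with a 95% CI taken from the CI for the slope.
- Otherwise: "If assumptions are not met, analysis will then be data-driven".

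Dose enters neither as a term in this model nor as a stratum for reporting half-life. The same section does compare the two active arms on antibody level at each time-point, by a Mann-Whitney test after a significant three-group Kruskal-Wallis test.

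Section 3.5 says how long the antibodies persist will guide the recommended dosing frequency, and gives the primary objective as "to assess the persistence of the MABs in the vagina and the systemic absorption at two different doses". Section 4 words the objective as retention in the vagina and names no dose contrast.

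**The concern.** Each woman receives one dose, so the participant intercepts absorb any difference in level between doses. What remains is a single slope for about 20 women. Nothing in the plan gives a half-life for the high-dose gel, a half-life for the low-dose gel, or the difference between them.

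The level comparisons do not fill this gap. The high-dose gel holds twice as much of each antibody per gram (Table 8-1), so levels at 24 h could differ by dose with identical half-lives, and a test at one time-point cannot tell the two explanations apart.

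If decline does depend on dose, the reported half-life lies between the two true values, and its CI may exclude one or both. That number is the one meant to inform dosing frequency.

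**Working it through.** The protocol gives no power, SD or expected half-life (section 10.1 says there is no information for power calculations), so there is no figure of the plan's own to reproduce. The half-lives and SDs below are assumptions.

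**Inputs from the protocol.** 30 women randomised 1:1:1 (sections 6.3 and 10.3.1), so about 10 per arm and 20 on active gel. Samples at 1, 8 and 24 h: mean 11, sum of squares (−10)² + (−3)² + 13² = 278 per woman.

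**Assumptions.** Complete data (60 observations), independent errors with residual SD 0.5, 0.75 or 1.0 on the natural-log scale, the same slope for all women within a dose, and tests at the 5% level (the protocol gives no level for its checks).

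**Degrees of freedom.** Time by participant: 19 and 60 − 40 = 20. A dose-by-time term added to the planned model: 1 and 60 − 22 = 38. Women's individual slopes compared between arms: 1 and 18.

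**Noncentrality.** With d the difference in slope between doses, all three tests have λ = 20 × (d/2)² × 278 / SD². For 6 v 9 h the slopes are 0.693/6 = 0.1155 and 0.693/9 = 0.0770, so d = 0.0385. At SD 0.5, λ = 5,560 × 0.01925² / 0.25 = 8.24.

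**Power to detect the dose difference** (noncentral F), at SD 0.5 / 0.75 / 1.0:

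| True half-lives | Planned check (19, 20 df) | Dose by time (1, 38 df) | Slopes by arm (1, 18 df) |
|---|---|---|---|
| 6 v 9 h | 19 / 10 / 8% | 80 / 46 / 29% | 78 / 44 / 28% |
| 6 v 12 h | 44 / 19 / 12% | 99 / 80 / 56% | 98 / 78 / 53% |
| 8 v 12 h | 12 / 8 / 6% | 56 / 29 / 18% | 53 / 28 / 18% |

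At smaller SDs the planned check does better: for 6 v 12 h its power is 67% at SD 0.4 and 93% at SD 0.3.

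**What the pooled half-life then says.** For 6 v 9 h the mean slope is 0.0963, a half-life of 0.693/0.0963 = 7.2 h. It sits 0.0193 from each dose's true slope. The CI half-width is about 2.023 × SD/√5,560 = 0.014, 0.020 and 0.027 for the three SDs, so at SD 0.5 the interval usually fails to reach a given dose's value. In simulated trials that passed the uniformity check, the pooled 95% CI covered a given dose's true half-life as follows (SD 0.5 / 0.75 / 1.0):

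| True half-lives | Pooled half-life | Check passes | Coverage of a given dose |
|---|---|---|---|
| 6 v 6 h | 6.0 h | 95 / 95 / 95% | 95 / 95 / 95% |
| 6 v 9 h | 7.2 h | 81 / 90 / 92% | 26 / 57 / 72% |
| 6 v 12 h | 8.0 h | 56 / 81 / 88% | 3 / 26 / 49% |

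**The case against.** Four arguments favour the plan as written.

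First, the primary endpoint (section 5.5.1) is antibody level, half-life is not a listed endpoint, and levels are summarised by arm and can be tested between doses at 24 h after the first dose and 12 and 36 h after the twelfth. That is a comparison of what is retained. This stands: a reader might infer that persistence is never compared between doses, and the protocol does not support that. What is missing is narrower, namely the rate of decline by dose.

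Second, under the exponential decay that section 10.2.2 assumes with a rate independent of dose, half-life does not depend on starting amount. The doses differ two-fold in the same gel-forming matrix, and the documents give no evidence that decline depends on dose. This also stands. A reader might infer that the pooled half-life describes neither dose, but that holds only if the slopes differ, which the documents neither show nor refute.

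Third, the pooled value is conditional on the uniformity check, and that check contains the dose contrast. True, so the plan is not blind to a dose difference. But the check is weak for it over most of the range above, a rejection would not point to dose as the cause, and the response to a rejection is left open.

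Fourth, the inputs are assumed, 6 v 12 h is an extreme case, and a detailed SAP, not seen here, may add half-lives by dose. The first two parts are accepted, and 6 v 9 h is therefore the main illustration. On the third, the protocol itself fixes the model, checks and estimator without dose.

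**Conclusion.** The point holds in a limited form. Section 10.2.2 imposes one slope per antibody across two randomised doses and plans no estimate or comparison of decline by dose, while section 3.5 sets out to assess persistence at both doses and to use persistence in choosing dosing frequency. The one check that could reveal a difference has about 8% to 19% power for 6 v 9 h, where a direct dose-by-time test has 29% to 80%. In the trials that pass the check, the pooled CI covers a given dose's true half-life about 26% to 72% of the time instead of 95%.

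These sizes rest on the assumed half-lives, log-SDs of 0.5 to 1.0, complete data and no slope variation between women within a dose. With smaller SDs the check works better, and with equal half-lives pooling costs nothing. The change is worth making because dose-independent decline is untested in what section 10.1 calls the first intravaginal use in humans.

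**What to change.** In section 10.2.2, add a dose-by-time term to the half-life model, or compare the women's individual log-concentration slopes between the two active arms (18 df), which also allows for slopes that vary between women. For each antibody, report the half-life with 95% CI at each dose and the between-dose difference in slope with its CI, whether or not that difference is significant. Keep the pooled half-life as a secondary summary.

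The cost is one model term and a few table lines, with no new samples or women. Each per-dose CI is about √2 = 1.4 times wider than the pooled one, because it rests on 10 women instead of 20. The report should also say that a non-significant dose-by-time result does not show equal half-lives: for 8 v 12 h even the direct test has only 56%, 29% and 18% power at the three SDs.

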## **10.3 Randomisation scheme and maintenance of blinding**

### **10.3.1 Randomisation code**

Randomisation will be carried out by the York Trials Unit, University of York. Subject numbers 01 to 30 will be randomised to Mabgel (high dose), Mabgel (low dose) or placebo using blocked randomisation of mixed block sizes. Randomisation will be in the ratio of 1:1:1. The randomisation program will be generated using Microsoft Visual Basic and a copy of the generated data stored in Microsoft SQL Server. The randomisation list will be posted to Polymun Scientific, Austria for the purposes of labelling the study gel. Personnel carrying out subsequent analyses will not have access to this list.

Participants will only be allocated a randomised subject number when they have provided informed consent to take part in the trial, and all screening tests have been carried out to ensure they meet the eligibility criteria. Subject numbers will then be allocated on a sequential basis at visit 2 after cervico-vaginal examination.

In order to maintain double-blinding, neither the CI nor the Investigators will have direct access to the randomisation codes.

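### Half-life comes from a common-slope model gated by a participant-by-time test: if decay varies between women, the interval is moderately short after a pass and no estimator is fixed after a failure

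*Protocol*

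**What the plan says.** Section 10.2.2 restricts the half-life analysis to participants who received active gel and to "observations at 1, 8, and 24 hours after the first dose". On log concentrations it specifies an "analysis of covariance model fitted with time as continuous predictor and participant as a categorical factor", which means a separate intercept for each woman and one slope for all of them.

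Two checks follow. "Linearity will be checked by including and testing a time squared term", and "Uniformity of the half life will be checked by testing an interaction between time and participant". No significance level is given for either. "If the assumptions are met, half-life will be estimated by" log(2) over the slope, with the ordinary model-based 95% interval. Otherwise "If assumptions are not met, analysis will then be data-driven".

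The same section says that a half-life has no useful meaning without exponential decay. It says nothing of that kind about half-lives that differ from woman to woman.

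**The concern.** The common-slope interval is built from scatter around one shared slope. It does not fully count differences in decay between women as sampling variation, and the plan relies on a small interaction test to rule such differences out. Section 3.5 says persistence in the lower genital tract is to inform dosing frequency, so the natural target is women in general and not only the women enrolled.

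For that target each branch has a weakness. After a pass, the interval may be too short. After a failure, no method is named and the choice is made with the data in view. Yet variation between women is an ordinary feature of pharmacokinetic data and does not stop one from estimating an average decay rate and its spread.

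**Working it through.** The protocol gives no half-life, variance or power figure (section 10.1 says there is no information for power calculations), so there is no stated figure to reproduce. The check is of how the planned procedure behaves.

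**Inputs from the protocol**
- Section 6.3: "We will aim to recruit and randomise 30 healthy HIV negative female volunteers". Section 10.3.1: "Randomisation will be in the ratio of 1:1:1". That gives about 10 per arm and 20 on active gel.
- Three times per woman, so 60 observations if complete. The mean time is 11 h, the centred times are -10, -3 and 13, and Sxx = 100 + 9 + 169 = 278 h².
- Common-slope residual df: 60 - 21 = 39. Interaction test: 19 df against 60 - 40 = 20 df. The 5% critical value is F = 2.137.

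**Assumed:** checks at the 5% level, normal errors, complete and detectable samples, half-life 4 or 8 h, between-woman CV of the decay rate 20, 30 or 40%, residual SD s of 0.5 or 1.0 natural-log units.

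**Formulas.** Let τ be the between-woman SD of the slope and λ = 278τ²/s².
- The true variance of the mean slope is (s² + 278τ²)/(20 × 278).
- The common-slope mean square has expectation s² + (19/39) × 278τ², so only about half of the heterogeneity enters the standard error.
- The interaction test rejects with probability P(F(19,20) > 2.137/(1 + λ)).

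**One case in full.** For a 4 h half-life, CV 30% and s = 1.0, the decay rate is 0.693/4 = 0.173 per h, τ = 0.052 and λ = 0.052² × 278 = 0.75. The threshold becomes 2.137/1.75 = 1.22, and the test rejects in 33% of trials.

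**Results.** Rejection is exact; coverage after a pass is simulated, 400,000 trials per value of λ.

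| Half-life, SD, CV | λ | Test rejects | Coverage after a pass |
|---|---|---|---|
| identical half-lives | 0 | 5% | 95% |
| 8 h, 1.0, 20% | 0.08 | 7% | 94.5% |
| 8 h, 1.0, 30% | 0.19 | 10% | 94% |
| 8 h, 1.0, 40%; 8 h, 0.5, 20%; 4 h, 1.0, 20% | 0.33 | 15% | 93% |
| 8 h, 0.5, 30%; 4 h, 1.0, 30% | 0.75 | 33% | 91% |
| 8 h, 0.5, 40%; 4 h, 1.0, 40%; 4 h, 0.5, 20% | 1.34 | 58% | 89% |
| 4 h, 0.5, 30% | 3.0 | 91% | 82% |
| 4 h, 0.5, 40% | 5.3 | 99% | 75% |

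The row for identical half-lives comes from a separate run of 200,000 trials. An interval from participant-level slopes (t on 19 df, no pretest) covers 95% in every row. With 18 women instead of 20 the picture hardly changes: at λ = 1, rejection is 41% instead of 44%, and coverage is 90% in both.

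**Failure by chance alone.** If both assumptions hold exactly and the checks are treated as independent, an antibody goes to the data-driven route with probability 1 - 0.95² = 9.8%. For at least one of three antibodies, also treated as independent, it is 1 - 0.95⁶ = 26.5%.

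**The case against.** **Half-life is not an endpoint.** Section 5.5 lists antibody levels at fixed times. Those are summarised and compared by rank tests that do not use this model, and no decision rule uses the half-life interval. This stands, and it limits the severity. A reader might infer that the primary endpoint has no valid analysis; the protocol does not support that.

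**The size rests on assumptions.** The protocol gives no variances, so the 7 to 99% range describes the assumed scenarios and not this trial. This also stands. The lowest coverages occur where the test almost always rejects: the 75% case passes in about 1% of trials. Over the whole grid, passing the test and then missing the true value happens together in at most 5.8% of trials. A reader might take the bottom rows as the likely coverage; they are not.

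**The target may be the women studied.** For the mean slope of these 20 women, which suits participant as a fixed factor, the interval is conservative, because its mean square contains heterogeneity that is not error for that target. This is correct. It does not answer the purpose in section 3.5, which looks beyond the women enrolled.

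**The unseen analysis plan may name a fallback.** It may. But the protocol itself fixes the common slope, the gate, the ordinary interval and the data-driven route, so the problem lies in what it states.

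**The sign.** A decay slope is negative, so log(2)/slope is negative as written. A reader might infer that a negative half-life would be reported. This is a slip of notation that any analyst would correct, and it adds nothing to the severity.

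**Conclusion.** The point holds with limits. If decay rates vary between women and the target is women in general, the gate does not protect the common-slope interval. Under the assumed values, coverage is about 89 to 94.5% wherever the test passes in at least 40% of trials. This is a moderate shortfall. It would be wrong to say that the interval is always too narrow: with identical half-lives coverage is nominal.

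With larger variation the main problem is the other branch. The test then usually rejects and the protocol names no estimator. That outcome is avoidable, since a mean decay rate with its spread remains interpretable when women differ.

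This should be fixed rather than must be fixed, because half-life is derived from the primary endpoint and is not itself listed. The figures assume complete, detectable samples, and values below detection cannot be logged.

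**What to change.** In section 10.2.2:

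1. Remove the participant-by-time test as a condition for estimating half-life.
2. Fit each active-arm woman's slope to her three log concentrations. Take the mean slope with a t interval over women (19 df if all 20 are complete), or use the equivalent random-slope mixed model if samples are missing.
3. Report half-life as -ln(2)/mean slope, transform the interval limits in the same way, and give the between-woman spread.
4. Keep the linearity check and state its significance level. In place of the data-driven wording, fix one fallback that respects the protocol's own view of non-exponential decay: report no single half-life, and give the decline over 1 to 8 h and over 8 to 24 h as participant-level changes in log concentration with t intervals.

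The cost is a change of wording, with no new data. If all women truly share one half-life, the interval is about 3% wider: t(19)/t(39) = 2.093/2.023 = 1.035.
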